### Measurements

General data collection procedures and the scope and timing of demographic data outcome collection are summarized in Tables 2 and 3 respectively.

**Table 2 Tab2:** Summary of data collection

	Enrollment	Baseline/Assessment	Follow-Up	Exit
CF or DRF Signed and Dated	X	X		
Subject Demographics	X	X	X	X
Outcome Measures	X	X	X	X
Medical History	X			
Assessment Details	X	X	X	
Patient Status	X	X	X	X
Events	X	X	X	X
Protocol Deviations	X	X	X	X

**Table 3 Tab3:** Summary of collected demographic and outcome data

Demographic measures	LBP Patients	Controls
Age	X	X
Gender	X	X
Pain episode duration (weeks)	X	X
Body Mass Index (BMI)	X	X
Employment (working vs not working)	X	X
Marital Status	X	X
Co-morbidities (categories)	X	X
Co-interventions - current medications (categories)	X	X
Co-interventions - (hospital admissions, doctor or other clinician visits, imaging, other diagnostic tests,	X	X
Patient outcomes		
LBP diagnosis (ICD-10) - clinician	X	
LBP – movement pattern classification (clinician)	X	
LBP – Movement Classifier	X	
QVAS - back	X	X
QVAS - leg	X	X
Oswestry Disability Index (ODI)	X	
START-Keele	X	
Fear Avoidance Behavior Questionnaire (FABQ)	X	
EQ-5D	X	X
Depression Anxiety Stress Survey 21 (DASS-21)	X	X
Patient perception of movement contribution to pain - single item	X	
Movement outcomes		
ViMove standard assessment (includes range of motion, speed, and timing of movement as described in “Measurements”)	X	X
30 s sit-to-stand test	X	X
40 m walk test	X	X

The dorsaVi ViMove system consists of two wireless tri-axial inertial measurement sensors containing accelerometers, gyroscopes, and magnetometers. These allow evaluation of movement in all three anatomical planes. Additionally, two wireless, bipolar, ViMove surface electromyography (sEMG) sensors will be placed on the subject’s low back via a disposable adhesive safe for human-use at standardized locations based on anatomy and subject height. Once these sensors are placed (at approximately the L3-vertebrae), the subject will be asked to move through a sequence of assessments (see Table 4).

**Table 4 Tab4:** ViMove (dorsaVi) Assessment

Posture / Movement performed by subject:	Instructions to the Subject
Standing – ‘normal’ posture (calibration)	● Warm up – walk at comfortable pace for 20 s. ● Stop and reach towards the ceiling as high as you can. ● Stand with feet hip distance apart. ● Look straight ahead. ● Now we are going to measure your posture ● Stand still whilst I count to 5.
Flexion (*subject chooses speed, using support for balance if required)*	We want to see how you bend forward. ● When I say go, bend forward as far as possible, hold for 3 s, and then return to the starting position. ● Repeat this × 3
Extension	We want to see how you bend backward. ● Cross your arms over your chest. ● When I say go, bend back as far as possible and then return to the starting position. ● Repeat this × 3
Lateral flexion - right	We want to see how you bend sideways. ● Place your arms by your side. ● When I say go, slide your *right arm* down your right leg as far as possible and then return to starting position. ● Repeat this × 3
Lateral flexion - left	We want to see how you bend sideways. ● When I say go, slide your *left arm* down your left leg as far as possible and then return to starting position. ● Repeat this × 3
Pelvic tilt in standing	We want to see how you move your pelvis and see if you can move it without moving the rest of your body. ● This is how you tip your pelvis forward (demo) and this is how you tip your pelvis back. One forward and one back counts as one total movement. Have a practice (max 10 s) and I will start recording your movement. ● I want you to do this at least 3 times.
Usual sitting posture (as demonstrated by subject)	Take a seat in your chair. Show us how you usually sit.
Poor sitting posture (as demonstrated by subject)	Now show us how you sit when you are sitting poorly.
Good sitting posture (as demonstrated by subject)	Now show us how you sit when you are sitting in a good position.
Pelvic tilt in sitting – through full range	We want to see how you move your pelvis in the chair and see if you can move it without moving the rest of your body. ● Sit to the front of the chair. ● Roll forward as far as possible and then roll back onto your Tailbone as far as possible. This is how you tip your pelvis forward (demo) and this is how you tip your pelvis back. Have a practice (max 10 s) and I will start recording your movement. ● I want you to do this at least 3 times.
40 m (4x10m) Fast Paced Walk Test	“*For this test, do the best you can by going as fast as you can, without running, but don’t push yourself to a point of overexertion or beyond what you think is safe for you*. *1. Start with both feet on the start line.* *2. On start, walk as quickly but as safely as possible, without running.* *3. Walk up to the end cone, turn around and walk back to the starting cone behind you, turn again and back to the end cone, then turn once more and return to the start cone again so that you walk the 10 m walkway 4 times in total.* *4. Get ready and START”.*
30 s sit-to-stand test	“*For this test, do the best you can by going as fast as you can but don’t push yourself to a point of overexertion or beyond what you think is safe for you*. *1. Place your hands on the opposite shoulder so that your arms are crossed at the wrists and held close across your chest. Keep your arms in this position for the test.* *2. Keep your feet flat on the floor and at shoulder width apart.* *3. On the signal to begin, stand up to a full stand position and then sit back down again so as your bottom fully touches the seat.* *4. Keep going for 30 s and until I say stop.* *5. Get ready and START”.*

Motion sensor data will evaluate range of motion, acceleration, and velocity of movement, lumbo-pelvic contribution to movement, and onset of lumbar/pelvic movement.Contribution of pelvis vs. lumbar movement is calculated as the peak lumbar angle divided by trunk peak angle at end-range trunk flexion. This is evaluated in the movement ‘Flexion’ as defined in Table 4.Onset of lumbar/pelvic movement is similarly evaluated in the ‘Flexion’ task. Start of the flexion was defined as the point at which the velocity of movement exceeds 7°/s. This definition is automatically detected by the ViMove software.

Motion data is automatically processed by ViMove as follows:Accelerometer and gyroscope readings are low-pass filtered with a zero-phase, second-order Butterworth filter, and cut-off frequency of 5 Hz [18]. Data is sampled at 20 Hz.

sEMG data is automatically processed by ViMove as follows:Data is sampled at a frequency of 300 HzA Band-Pass Filter is applied at 20 − 300 HzHigh-Pass Filter set to 20 Hz to reduce baseline drift and ECG componentsLow-Pass Filter set to 300 Hz to create an envelope of the signal which is then anti-aliased and down-sampled.This signal is then used to calculate a moving root-mean-square average.

LBP patients and non-LBP controls will be assessed at enrolment (baseline). LBP patients will then then be followed up at 6 and 12 months (see Fig. 1).

**Fig. 1 Fig1:**
[figure not shown]
Schematic of study design

### Statistical analysis

Baseline characteristics of LBP and controls will be reported descriptively as means (and standard deviations) or medians (and inter-quartile ranges) for continuous variables, or frequencies (and percentages) for binary variables. Groups will be compared using the independent 2-group t-test, Mann-Whitney U test, or Chi^2^–test respectively.

#### Comparison of range of movement and secondary outcomes between LBP subjects and non-LBP controls

Continuous primary and secondary outcomes will be compared between LBP and control groups using linear regression methods, and categorical outcomes will be compared using logistic regression. Models will be adjusted for baseline outcome scores (ANCOVA) plus matching variables and other characteristics found to be significantly different between groups at baseline. Between-group comparisons will be undertaken at baseline and each follow up. Within group differences in outcomes between baseline and follow up will also be examined. Residual plots will be used to check goodness of fit of regression models and, where necessary, power transformation of outcomes undertaken to improve model fit.

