### Subject selection

Subjects with LBP will be included if they fulfil the following criteria:Subject or legally authorized representative provides written authorization and/or consent per institution and geographical requirementsSubject with a predominant complaint of LBP of any duration, with a minimum daily pain average visual analogue score (VAS) ≥ 30/100Subject is intended to be assessed with the eligible product

Exclusions to enrollment are:Unable to be available for study follow-upsExclusion criteria required by local lawMovement assessment is contraindicated for any reason.Currently enrolled in or plans to enroll in any concurrent drug and/or device study that may confound resultsBody mass index ≥35 kg/m^2^

Controls will be recruited using study advertisement flyers posted on campus at the George Washington University, local gymnasiums, recreational centers, via word of mouth, and email list servers associated with educational programs within The George Washington University School of Medicine and Health Sciences. Subjects will be screened by phone for the presence or history of LBP (no current LBP and no history of LBP lasting longer than 3 months in the past 12 months) as well as other exclusion criteria listed above. Controls will be age and sex-matched with LBP patients on a one-to-one basis.

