#### Association between demographic and clinical characteristics and range of movement outcomes in LBP subjects

Pearson correlation coefficients will be used to assess the univariable association between range of movement and various back pain subject characteristics. Multivariable associations will also be assessed using multivariable Pearson correlation coefficients and multivariate linear regression analysis. In determining multivariable models, collinearity between potential variables will first be assessed and variables where high collinearity will be excluded.

The focus on all data analyses will be on those registry participants with complete data. However, we will report rates and reasons for missing data and, where appropriate, consider imputation of missing cases using appropriate statistical methods.

All inferential analysis results will be reported as mean differences and 95% confidence intervals. We will report *P*-values to three decimal places with P-values less than 0.001 reported as *p* < 0.001. All statistical tests will be performed using two-sided tests at the 0.05 level of significance. No formal adjustment of the level of significance for testing will occur, but P-values will be interpreted accordingly, considering the multiple testing outcomes. An analysis will be undertaken at the end of the phase I, upon completion of enrolment of the age and sex-matched cohorts, prior to proceeding with enrolment of phase II of the registry.

All analyses will be undertaken using STATA version 14 [17].

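### Choosing covariates by baseline significance tests is likely to bring consequences of back pain into the LBP-versus-control model and, to a lesser degree, leaves BMI to chance

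*Protocol article*

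**What the plan says.** The section comparing LBP subjects with controls fixes some covariates: "Models will be adjusted for baseline outcome scores (ANCOVA) plus matching variables". It then adds "other characteristics found to be significantly different between groups at baseline". The opening paragraph of the statistical analysis section names the tests that decide this: "Groups will be compared using the independent 2-group t-test, Mann-Whitney U test, or Chi^2^–test respectively". The level is set at the end of the statistical section: "All statistical tests will be performed using two-sided tests at the 0.05 level of significance". The article names no other covariate in advance and excludes no candidate.

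Table 3 (Measurements) lists the candidates collected in both groups. Under demographic measures it has BMI and employment, but also "Pain episode duration (weeks)", "Co-interventions - current medications (categories)" and a row for hospital admissions, clinician visits, imaging and other diagnostic tests.

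Under Subject selection, patients need a daily average pain score of at least 30/100, while controls must have no current LBP and no episode longer than 3 months in the past 12 months. Controls are matched on age and sex only and come partly from "local gymnasiums, recreational centers".

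**The concern.** In a non-randomized comparison, whether to adjust for a variable depends on its causal place, not on a p-value. A significance test cannot tell a confounder from a consequence of the exposure, and here it favours the consequences because they differ most between groups. Pain duration comes close to restating group membership. Medication and health-care use should differ widely between patients enrolled at a spine pain center and a physical therapy practice and controls without current pain.

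Adjusting for such variables changes the question. The stated aim is to describe how movement differs between people with and without LBP; the adjusted coefficient describes the difference at equal treatment and health-care use. It is also less precise, because the covariate and the group carry much of the same information. A null result could then not be told apart from over-adjustment.

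The opposite fault is milder. BMI could plausibly differ between clinic patients and controls recruited partly from gyms. It is neither matched nor named as a covariate, so it is adjusted for only if its test happens to reach 0.05.

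**Working it through.** **The plan's own figure.** Inputs from the Sample size section: effect 0.40 SD, two-sided alpha 0.05, 90% power, 132 per group.

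- Standard error of the unadjusted difference: sqrt(2/132) = 0.123 SD.
- Noncentrality: 0.40/0.123 = 3.25. Power from the noncentral t with 262 degrees of freedom is 0.899; the normal approximation gives 0.901.
- The 132 per group is reproduced. It is sized on a contrast with no loss of precision from covariates correlated with group.

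**What the rule selects.** A t-test with 132 per group is significant when the observed standardized difference exceeds 1.969 × 0.123 = 0.24 SD. The chance of selection by true difference is:

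| True difference (SD) | 0.10 | 0.20 | 0.30 | 0.40 | 0.50 | 1.00 |
|---|---|---|---|---|---|---|
| Selected | 13% | 37% | 68% | 90% | 98% | about 100% |

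A variable that differs strongly because of LBP is almost certain to enter. A modest confounder usually is not.

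**Loss of precision from a consequence unrelated to movement.** The article gives no prevalences. Assume every patient and a proportion p of controls report a recent clinician visit. With equal groups, the overall proportion is m = (1 + p)/2, the correlation of the covariate with group is phi = (1 − p)/(2·sqrt(m(1 − m))), and VIF = 1/(1 − phi²). Power uses the standard error 0.123 × sqrt(VIF).

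| p | m | phi | VIF | Power for 0.40 SD |
|---|---|---|---|---|
| 0.20 | 0.60 | 0.816 | 3.00 | 46% |
| 0.30 | 0.65 | 0.734 | 2.17 | 59% |
| 0.50 | 0.75 | 0.577 | 1.50 | 75% |

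**Loss of the contrast when the consequence is related to movement.** Let the covariate differ by D between groups (within-group SD units) and correlate r with movement within groups, in the direction that accounts for part of the group difference. The adjusted effect is 0.40 − r·D, VIF = 1 + D²/4, and the standard error is sqrt((2/132)(1 − r²)·VIF). Assume D = 1, so VIF = 1.25.

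| r | Adjusted effect (SD) | Standard error | Power |
|---|---|---|---|
| 0.1 | 0.30 | 0.137 | 59% |
| 0.2 | 0.20 | 0.135 | 32% |
| 0.3 | 0.10 | 0.131 | 12% |

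**BMI left to a test.** Simulation of 10,000 data sets per scenario, 132 per group, no true group effect, confounder imbalance 0.1-0.3 SD and correlation with the outcome 0.3 or 0.5 (all assumed):

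- A 0.20 SD imbalance goes unadjusted in about 63% of studies (100% − 37%).
- Average bias under the significance rule is about 0.02-0.04 SD. In the data sets where the confounder is missed it is 0.02-0.08 SD.
- Type I error under the rule is 4.6-5.6%.
- With the confounder always in the model, mean bias is about 0 and type I error is 4.4-5.3%.

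**The case against.** The strongest reply is that the article never defines the candidate characteristics. An analysis plan that is not shown could narrow the list, so the amount of over-adjustment cannot be read from the text. That stands as a limit on size. It does not remove the point: the rule is stated as what will be done, no candidate is excluded, and the likely consequences of LBP sit in the demographic block of Table 3. The collinearity screen does not help, since it is written for the association analysis within LBP subjects and not for the between-group models.

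Several stronger readings are tempting, and the article does not support them.

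- **Pain score as a covariate.** Assuming 50 (SD 15) against 3 (SD 5), adding it would give VIF 5.4 and power of about 28%. But Table 3 files the pain scale under patient outcomes, and nothing says outcomes count as characteristics. The figure is no part of the conclusion.
- **Employment as a plain consequence.** Work status can precede pain, and controls come partly from a university. It may confound as well as follow.
- **A large bias from BMI.** The 63% is a chance of non-selection, not a measure of harm. Bigger imbalances are mostly caught, and excluding BMI of 35 or more in both groups narrows the range.
- **Fitness left out by this rule.** Table 3 lists no fitness or activity history, so its absence from the model does not come from the rule.
- **Standard errors made invalid by selection.** For one confounder of this kind, type I error stayed near 5%, so no material inflation is shown.

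**Conclusion.** The point holds, and over-adjustment carries it. Followed as written, the rule is likely to put pain duration, medication or health-care use into the primary LBP-versus-control model. Under the assumed visit prevalences, power for 0.40 SD falls from 90% to 46-75% even if the covariate has nothing to do with movement. Under an assumed 1 SD group difference and r of 0.1-0.3, between a quarter and three quarters of the contrast is removed (0.10/0.40 to 0.30/0.40).

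The prevalences, D and r are not in the article, so these figures show scale and are not predictions. The loss of precision needs only a strong association between covariate and group. The attenuation also needs an association with movement, and its direction depends on the sign of that association. The BMI half is secondary, with average bias of about 0.02-0.04 SD, and would not make the case alone.

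**What to change.** Replace the significance rule with a covariate set named in advance and used for every movement outcome: age, sex and BMI. State that pain duration, pain scores, medication, health-care use and imaging are not adjusted for in the LBP-versus-control contrast. Keep the baseline table descriptive, with no role in choosing the model.

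Add site only if both groups are assessed at each site. The article names two clinical centers for the registry but does not say where controls are assessed; if site tracks group, forcing it in brings back the same variance inflation. Put employment in a sensitivity model, because its causal place is uncertain.

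The cost is a change of wording, made before the phase I analysis. BMI is already collected in both groups, and 132 per group can stand. The price is slightly less freedom to respond to an unexpected imbalance, which a labelled sensitivity analysis can cover.

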**Methods:**

This ongoing, non-randomized, prospective post-market registry will consist of two groups: patients with LBP, and age and sex-matched controls without LBP. We will seek to recruit 132 subjects in each group. Data collection will take place in two phases: (1) baseline assessment of LBP patients and matched controls; (2) assessment of LBP patients at 6 and 12-months follow up. The primary outcome measure will be differences in movement patterns between those with LBP and those without LBP. Secondary outcomes will include differences in patient reported outcomes including pain, disability and quality of life.

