## Methods/design

This is an ongoing, non-randomized, prospective post-market registry consisting of two groups: patients with LBP, and age and sex-matched controls without LBP. We will recruit a total of 132 subjects in each group. B-PAM has a flexible design to allow new dorsaVi products to be added to the registry following their market release. Data collection will take place in two phases: (1) baseline assessment of LBP patients and matched controls; (2) assessment of LBP patients at 6 and 12-months follow up.

Reporting and data analysis of the B-PAM registry will be undertaken in accord with The Strengthening the Reporting of Observational Studies in Epidemiology (STROBE) guidelines for reporting observational studies [14].

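### Between-group models are planned at 6 and 12 months with adjustment for the baseline outcome, but controls are assessed only at baseline, so the models fail as written

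*Protocol article*

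**What the plan says.** Two parts of the protocol article bear on this.

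**Analysis.** The subsection comparing LBP subjects with controls sets linear regression for continuous primary and secondary outcomes and logistic regression for categorical ones. It then says: "Models will be adjusted for baseline outcome scores (ANCOVA) plus matching variables and other characteristics found to be significantly different between groups at baseline". The next sentence is: "Between-group comparisons will be undertaken at baseline and each follow up". It also plans to examine change from baseline within groups.

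**Schedule.** Methods/design describes the two data-collection phases as "1) baseline assessment of LBP patients and matched controls; (2) assessment of LBP patients at 6 and 12-months follow up", and the Abstract gives the same two phases. The text after Table 4 in Measurements has both groups assessed at enrolment and continues: "LBP patients will then then be followed up at 6 and 12 months". No section gives controls a second visit.

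**The concern.** ANCOVA with a baseline covariate needs two measurements per person in both groups. Controls have one. The adjustment therefore suits neither time point as written: at baseline the outcome would be adjusted for itself, and at follow-up one of the two groups has no outcome.

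This subsection governs the primary outcome, the difference in movement patterns between people with and without LBP. If the rule cannot be run, the analyst must replace it with another model, and the plan does not say which. For the baseline contrast the replacement is fairly obvious. For 6 and 12 months it is not: the choices are no between-group result, or a comparison with control values taken at another time. Either would be decided after data are in hand.

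**Working it through.** **Inputs**
- 132 per group, effect size 0.40, 90% power, alpha 5% (Sample size section); two-sided tests (Statistical analysis).
- One-to-one matching on age and sex (Subject selection).
- Control assessments: baseline only. LBP assessments: baseline, 6 and 12 months (Abstract, Methods/design, Measurements).

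**1. The plan's own figure**

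n per group = 2 × [(z₀.₉₇₅ + z₀.₉₀) / d]² = 2 × [(1.960 + 1.282) / 0.40]² = 131.34, rounded up to 132. Power at 132 per group is 0.901. The stated figure is reproduced. It is the size for a plain two-group comparison of means at one time point, with no baseline covariate and no repeated measures.

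**2. Follow-up model (6 or 12 months)**

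Model: Y_followup = a + b·group + c·Y_baseline.

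Scheduled rows: 132 LBP and 0 controls. Group equals 1 in every row, so its column equals the intercept column. The design matrix has 3 columns and rank 2, so b is not identified. Adding age, sex or other covariates does not help, because group still does not vary.

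**3. Baseline model, read literally**

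Model: Y_baseline = a + b·group + c·Y_baseline.

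The exact solution is a = 0, b = 0, c = 1, with residual sum of squares 0 and R² = 1, whatever the true group difference.

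This was checked on one simulated data set of 132 per group, using the Table 1 standing-flexion values for ages 30–39 (mean 46, SD 11) and a true difference of −4.4:

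| Model | Group coefficient | R² |
|---|---|---|
| Group + baseline outcome | 0 (about −1e−13) | 1 |
| Group only | −5.42 (SE 1.23) | not computed |

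For a binary outcome the literal logistic model is different: the covariate predicts the outcome perfectly and no finite maximum-likelihood estimate exists. The zero coefficient is a result for linear models only.

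**4. Could the control baseline value stand in at follow-up?**

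If so, outcome equals covariate for all 132 controls. The ANCOVA group coefficient is

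b = (mean Y_LBP − mean Y_C) − c × (mean X_LBP − mean X_C), with mean Y_C = mean X_C,

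which rearranges to

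b = (mean Y_LBP − mean X_LBP) + (1 − c) × (mean X_LBP − mean X_C).

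This is the LBP group's own change plus a fraction of the baseline gap. It is not a between-group difference at 6 or 12 months. Without the baseline covariate, the comparison of LBP follow-up values with control baseline values is estimable, but it is non-concurrent and the article does not describe it.

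**5. Does any other text schedule control follow-up?**

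Table 2 has a follow-up column that is not split by group. Subject selection screens controls against the listed exclusions, which include being unavailable for follow-up. Neither sets a control visit, and the three explicit schedule statements point the other way.

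**The case against.** The strongest reply concerns the baseline part. Adjusting for a baseline score ordinarily refers to a post-baseline outcome, so the authors may never have meant the term for the baseline model. Two places fit that reading: the sample size is a plain two-group calculation, and an analysis is planned at the end of phase I, before follow-up data are due. Removing the self-covariate leaves what the same sentence already names: group, matching variables and characteristics that differ at baseline. An R² of 1 would be noticed at once. This largely stands, and it limits the baseline part to a wording fault. It does not rescue the plan, because the follow-up models, where the ANCOVA term would belong, are the ones with no control outcomes.

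A second reply is that the Background presents the registry as a source of normative as well as follow-up data, so LBP follow-up values may be meant to be set against a fixed control reference. That is plausible and computable without the baseline covariate, but the analysis section does not say it.

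A reader might also infer three stronger points that the document does not support.
- **That the primary question cannot be answered, or would be reported as null.** The baseline data in both groups will exist, and the sample size suits an unadjusted contrast.
- **That disability is an impossible between-group outcome because the ODI is collected in LBP patients only.** This rests on one sentence in the Abstract: "Secondary outcomes will include differences in patient reported outcomes including pain, disability and quality of life". That sentence does not say between groups. The between-group question in the Background leaves disability out, and Table 3 agrees with it. The ODI can serve the within-group analysis.
- **That the back-pain contrast is an error because eligibility fixes it.** The contrast is predictable, but it can be computed and contradicts nothing.

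**Conclusion.** The point holds for the contradiction between the analysis section and the visit schedule. With 0 of 132 controls scheduled at 6 or 12 months, the between-group effect at follow-up is not estimable under any covariate set. At baseline the adjustment rule, taken literally, forces a group coefficient of 0 in every linear model and perfect prediction in every logistic one; an analyst would see this and drop the term, but the plan should not depend on that.

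This assumes that the Abstract, Methods/design and Measurements sections state the schedule correctly and that the baseline adjustment applies to all the between-group models, as its wording implies. If the adjustment was meant for follow-up only, the baseline fault disappears and the follow-up fault remains. If controls are in fact to be followed up, the analysis at follow-up becomes possible and the three schedule statements are wrong. On each of these readings the text needs reconciling. The 132 per group and 90% power stand for the baseline comparison.

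**What to change.** Reword the analysis subsection as follows.

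1. Make the between-group comparison at baseline only, with group, the matching variables and the other planned covariates, and with no baseline-outcome term.
2. Analyse the 6- and 12-month data as change within LBP patients, which the subsection already plans.
3. If LBP follow-up values are to be compared with the single control assessment, call this a non-concurrent reference comparison and omit the baseline-outcome covariate.
4. If control follow-up was intended, correct the Abstract, Methods/design and Measurements sections instead, and keep ANCOVA for the follow-up models only.

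Items 1 to 3 cost a few sentences, with no extra participants, visits or change to the sample size. Item 4 would add control visits and bring loss to follow-up among controls into the plan.
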